## Abstract

**Background:**

Patients with significant multimorbidity and other factors that make healthcare challenging to access and coordinate are at high risk for poor health outcomes. Although most (93%) of Veterans’ Health Administration (VHA) patients at high risk for hospitalization or death (“high-risk Veterans”) are primarily managed by primary care teams, few of these teams have implemented evidence-based practices (EBPs) known to improve outcomes for the high-risk patient population’s complex healthcare issues. Effective implementation strategies could increase adoption of these EBPs in primary care; however, the most effective implementation strategies to increase evidence-based care for high-risk patients are unknown.

The high-RIsk VETerans (RIVET) Quality Enhancement Research Initiative (QUERI) will compare two variants of Evidence-Based Quality Improvement (EBQI) strategies to implement two distinct EBPs for high-risk Veterans: individual coaching (EBQI-IC; tailored training with individual implementation sites to meet site-specific needs) versus learning collaborative (EBQI-LC; implementation sites trained in groups to encourage collaboration among sites). One EBP, Comprehensive Assessment and Care Planning (CACP), guides teams in addressing patients’ cognitive, functional, and social needs through a comprehensive care plan. The other EBP, Medication Adherence Assessment (MAA), addresses common challenges to medication adherence using a patient-centered approach.

**Methods:**

We will recruit and randomize 16 sites to either EBQI-IC or EBQI-LC to implement one of the EBPs, chosen by the site. Each site will have a site champion (front-line staff) who will participate in 18 months of EBQI facilitation.

**Analysis:**

We will use a mixed-methods type 3 hybrid Effectiveness-Implementation trial to test EBQI-IC versus EBQI-LC versus usual care using a Concurrent Stepped Wedge design. We will use the Practical, Robust Implementation and Sustainability Model (PRISM) framework to compare and evaluate Reach, Effectiveness, Adoption, Implementation, and costs. We will then assess the maintenance/sustainment and spread of both EBPs in primary care after the 18-month implementation period. Our primary outcome will be Reach, measured by the percentage of eligible high-risk patients who received the EBP.

**Discussion:**

Our study will identify which implementation strategy is most effective overall, and under various contexts, accounting for unique barriers, facilitators, EBP characteristics, and adaptations. Ultimately this study will identify ways for primary care clinics and teams to choose implementation strategies that can improve care and outcomes for patients with complex healthcare needs.

**Trial registration:**

ClinicalTrials.gov, NCT05050643. Registered September 9th, 2021, https://clinicaltrials.gov/study/NCT05050643

**Protocol version:**

This protocol is Version 1.0 which was created on 6/3/2020.

Contributions to the literature
The first study to compare the effectiveness of Evidence-Based Quality Improvement (EBQI) conducted individually with one site or conducted with a group of sites.Implementation of evidence-based practices to improve care for high-risk patients in primary care.

## Background

Patients who are at the highest risk for hospitalization (“high-risk patients”) are a heterogenous subset of patients who have significant multimorbidity and pose the most significant medical challenges within any healthcare organization [1]. These patients are at high risk for poor health outcomes and account for the majority of the Veterans Health Administration (VHA) healthcare costs [2], similar to other healthcare systems [3, 4]. Previous Medicare demonstrations, such as advanced primary care home models called Comprehensive Primary Care Plus (CPC +), have shown that caring for high-risk patients can be challenging despite financial alignment that promotes coordination of care delivery [5]. Primary care teams bear most of the responsibility in caring for complex patients; in VHA over 93% of high-risk Veterans are managed by general primary care teams, despite the availability of specialized primary care teams for patients with advanced health conditions [6]. Yet, complex, high-risk patients often do not receive the most effective evidence-based care within general primary care teams [7].

Many of the evidence-based practices (EBPs) have been ineffective in the management of high-risk patients due to the lack of EBPs that properly address multimorbidity— most EBPs focus on a single problem [8, 9]. However, there are a few EBPs that have shown to be effective for high-risk patients in geriatrics and other specialized settings, such as comprehensive assessments, individualized care plans, and care coordination among the multidisciplinary team members [10–12]. Evidence also supports patient-centered approaches to support self-management for high-risk patients with competing medical and self-care demands, including shared decision making and health coaching [12–14]. However, primary care teams have not implemented these EBPs widely [15, 16]. Despite the availability of these effective practices, the most effective implementation strategies to increase uptake of EBPs for high-risk patients in primary care are unknown. EBQI has been used successfully to implement complex EBPs in VA primary care, such as the patient-centered medical home model [17] and primary care-mental health integration [18, 19]. EBQI is, in fact, a bundle of implementation strategies that emphasizes a systematic approach to developing a researcher-clinical partnership that engages national, regional, and local-level senior organizational leaders and local QI teams in adapting and implementing EBPs in the context of prior evidence and local practice conditions [17]. Core elements of EBQI include engaging multi-level multidisciplinary stakeholders in evidence-based agenda setting (developing a “QI Roadmap”), training clinical champions in QI methods to meet agenda goals, and practice facilitation [17, 18, 20, 21]. The theoretical basis underlying EBQI elements includes theories of organizational change [22–25], clinical quality improvement, [26–28] complex adaptive systems [25], and diffusion of innovation [29]; each element can be mapped to documented implementation strategies [30]. However, beyond these core elements, EBQI initiatives have widely varied in the extent and types of interactions with implementation facilitators, specifically in practice facilitation and training. Some initiatives have combined EBQI core components with individual ongoing consultation [17, 20], which can require significant researcher and quality coordinator time and resources. Other VHA EBQI initiatives have used across-site learning collaboratives (i.e., depression collaborative care [18, 19] and opioid use disorder [31]), which may require fewer resources and impact a greater number of health professionals. While both variations have been effective, individual site-level consultation has never been empirically compared with learning collaboratives; implementers lack guidance on which of these strategies are effective in what setting.

## Methods

This study uses a mixed-methods type 3 hybrid implementation-effectiveness evaluation using a Concurrent Stepped Wedge design, evaluation of two separate interventions in different clusters, [32] to compare the two variants of EBQI aimed at increasing reach of the proposed EBPs (CACP or MAA). The Practical, Robust Implementation and Sustainability Model (PRISM) framework (Fig. 1) [33, 34] will guide the planning, implementation, and evaluation of the RIVET Program. The PRISM framework specifies contextual factors which align well with the components of our implementation strategies, and which will guide our evaluation of factors that influence Reach, Effectiveness, Adoption, Implementation, and Maintenance (RE-AIM) outcomes [34]. The Consolidated Framework for Implementation Research (CFRI) framework will identify implementation determinants, i.e., barriers and facilitators to implementation.

**Fig. 1 Fig1:**
[figure not shown]
RIVET implementation timeline for each site

### Evidence‑based practices (EBPs)

We selected two EBPs that guide primary care teams to identify modifiable needs among high-risk patients through standardized assessments and utilize the expertise of the multidisciplinary staff in the primary care team: Comprehensive Assessment and Care Plan (CACP) and Medication Adherence Assessment (MAA).

#### EBP Comprehensive Assessment and Care Plan (CACP) for high-risk patients

The CACP is an assessment that helps the primary care team to develop an individualized treatment plan based on identified needs for high-risk patients of any age [35]. It was adapted from the Comprehensive Geriatric Assessment (CGA), which has been shown in multiple randomized control trials (RCTs) to lead to improved outcomes for older adults with complex care needs [36, 37]. According to meta-analyses, the CGA has consistently led to improved outcomes for frail, older adults, such as decreased mortality (OR 0.86, 95% CI 0.75–0.98), decreased readmissions (OR 0.88, 95% CI 0.79–0.98), and decreased length of stay (1.63–40.7 days in intervention group vs 1.8–42.8 days in usual care) compared to those who did not receive the CGA [38–40].

While the CGA assesses several domains that are important for complex patients, some domains may not be broadly applicable to high-risk Veterans of all ages (i.e., nutrition, vision, hearing, continence). According to our analyses, half of high-risk Veterans are younger than 65 years old and have greater psychiatric comorbidities than older high-risk Veterans [6]. We added domains to specifically assess for modifiable risk factors that are common among high-risk Veterans (e.g., transportation assistance, health literacy, behavioral health symptoms, and coordination with non-VHA healthcare systems) [41–43]. The CACP screening questions are taken from standard sources, including the National Academy of Medicine Recommendations for High-Need Patients [44] and the Protocol for Responding to and Assessing Patients’ Assets, Risks, and Experiences (PRAPARE) [45].

The CACP prompts the primary care team member to explore identified risk factors further or to refer to another team member for an in-depth assessment if needed. After the assessment, the CACP is then used to guide the development and implementation of an individualized treatment plan that addresses the patient’s health-related needs in the context of the patient’s preferences [10]. The treatment plan can be coordinated and monitored through team huddles (consisting of the primary care provider, nurses, clerk) or monthly interdisciplinary team meetings.

#### EBP Medication Adherence Assessment (MAA)

High-risk Veterans often experience complicated medication regimens, potential side effects, and other known barriers to medication adherence [46]. Medication nonadherence represents a common problem among multimorbid patients [47], and is one of the largest contributors to preventable emergency department visits and hospitalizations among high-risk Veterans. Many approaches to improving medication adherence are limited by a focus on particular diseases rather than the entire medication regimen and by a focus on the healthcare providers’ point of view, rather than on patients’ goals and agency around medication taking [48].

A standardized Medication Adherence Assessment (MAA) guides primary care teams to assess for barriers and challenges to medication adherence through open-ended questions and enables primary care teams to understand high-risk patients’ goals and preferences and better impact medication-taking behaviors across the patients’ medication conditions [12, 13]. The MAA prompts the clinician to employ specific strategies around adherence and potentially use motivational interviewing or health coaching if the patient is ambivalent about taking a medication. Health coaching has emerged as an effective, patient-centered, collaborative approach to understand patient goals and preferences and enhance patients’ adherence to modifiable health behaviors [49]. Health coaching is a type of cognitive-based behavior change technique that employs motivational interviewing and goal-setting to guide the patient to change health behaviors, such as diet, exercise, and medication adherence [49]. Meta-analyses have shown that cognitive-based behavior change techniques (e.g., health coaching) to improve medication management are associated with an effect size of 0.34 (95% CI 0.23–0.46) on improved medication adherence [50]. 

### EBQI Implementation strategies

The high-Risk VETeran (RIVET) Program will compare two variants of Evidence-Based Quality Improvement (EBQI)—practice facilitation through Individual Consultation (IC) or through Learning Collaboratives (LC) to determine which of the two is the most effective and less costly implementation strategy and explore which is better suited for which contexts.

#### Individual Consultation (IC)

Individual consultation, often described as coaching or supervision, is endorsed by implementation experts as an effective implementation strategy in and of itself. In RIVET, external facilitators from the study team will provide training to QI participants, who are front-line primary care staff, from an individual medical facility. The RIVET IC will provide regular individualized EBQI training and coaching to implement the EBP. Consultation allows experts to tailor complex skills and training to needs of the organization and to the QI participants, using active learning and providing practice opportunities [51]. It also provides QI participants with problem-solving skills and accountability [51]. Literature has demonstrated increased uptake and adherence to EBPs and increase sustainability with IC [51, 52].

#### Learning Collaboratives (LC)

Learning collaboratives are also widely used in healthcare settings and are an effective implementation strategy [30]. The RIVET learning collaboratives consists of external facilitators from the study team providing quality improvement training to QI participants from multiple sites in a group, and encourages interaction and collaboration among QI participants (e.g., providing feedback to each other). The effectiveness of learning collaboratives vary, but generally, they have demonstrated improvement in health professionals’ knowledge, problem-solving skills and attitude, and teamwork [53]. The mechanisms by which learning collaboratives may be effective include factors within an organization and factors between multiple organizations. In terms of factors within an organization, participation in learning collaboratives may increase staff confidence in using data to make decisions and to problem solve, increase accountability by making standards explicit, promote peer reflection, and facilitate teamwork, shared responsibility, and joint problem solving [53]. Mechanistic factors between organizations include normative pressure from peers, friendly competition, a platform for capacity building, and collaboration with other sites [53].

### Site selection and eligibility

We will implement the EBPs at 16 primary care sites, targeting those with high ambulatory care-sensitive hospitalization rates. Each site will be implementing a single EBP. Implementation strategies are randomized by site. Site implementation consists of four overlapping cohorts of four sites (three randomized to LC and one to IC); all will undergo 18-months of RIVET facilitation (see Figure#1). Time periods without active implementation will serve as the usual care periods for EBQI strategies. Usual care sites will receive Office of Primary Care educational campaigns and dissemination of tools for high-risk patients among primary care teams. VHA regional leaders or VHA facility leaders will select the EBP for primary care sites to implement.

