#### Reach

Reach is defined in this study as the proportion of high-risk patients on each study team’s panel that received one of the EBPs during the 18-month implementation period. See Table 2 for details on included reach measures. We define “high-risk patients” using a VHA-specific risk score called the Care Assessment Need score, previously developed and validated by VA through machine-learning to predict a patient’s risk for a VHA hospitalization or mortality [54]. We define ‘receipt’ as having the EBP assessment at least partially documented in the electronic health record (EHR). We will also examine the patient characteristics (sociodemographic, Elixhauser comorbidity score [66]) of eligible patients who did vs. did not receive the EBP.

**Table 2 Tab2:** Reach and effectiveness outcomes metrics

	**Reach** **(Primary Outcome)**	**Proximal Care Process Impacts**	**Patient and Provider Impacts**	**Clinical Quality and Outcomes**
EBP 1 CACP	Proportion of site-assigned patients in the top 10% of CAN-hospitalization scores that receive the EBP	• Number and type of referrals generated • Referrals completed by patient • Number of primary care social worker, pharmacist, nurse, integrated MH encounters	• Comprehensiveness of Care (Patient Survey^a^/SHEP) • Self-Management Support (Patient Survey^a^/SHEP) • Primary Care provider experience and perceived support for high-risk patient care (Clinician Survey)	• VHA ACS-related and total acute hospitalizations • VHA ACS-related and total emergency department visits
EBP 2 MAA		• Number and type of referrals or actions documented receiving the EBP • Number of primary care pharmacist, social worker, nurse, integrated MH encounters	• Providers Discuss Medication Decisions/Medication Comprehensiveness (Patient Survey^a^/SHEP) • Self-Management Support (Patient Survey^a^/SHEP)	• Medication adherence (Patient Survey^a^) • Adherence for DM, HTN, HL, MH medications (VHA Pharmacy Data) • HEDIS measures for DM, HTN, HL management

*ACS* Ambulatory care-sensitive, *EBP* Evidence-based practice, *CACP* Comprehensive Assessment and Care Planning, *CAN* Care Assessment Need, *DM* diabetes mellitus, *HTN* hypertension, *HEDIS* Healthcare Effectiveness Data and Information Set, *HL* hyperlipidemia, *MAA* Medication Adherence Assessment, *MH* Mental Health, *PDC* proportion of days covered, *SHEP* Survey of Healthcare Experiences of Patients

^a^Refers to patient survey referenced in the Methods

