#### Effectiveness

EBP effectiveness measures will include type of referrals or actions generated by each EBP, and whether they were completed, as measured by EHR template use, administrative consult data, and encounters. We will also use administrative EHR data to measure number of patient encounters with primary care team members (social work, pharmacist, nurse, integrated mental health), as an indicator of engagement of primary care teams for high-risk patient care. Impacts of RIVET on patient experience will be evaluated with a patient survey that includes measures (described above) of satisfaction and access to resources and support for caring for high-risk patients. We will also assess clinical performance metrics that are expected to be directly impacted by each EBP. For both EBPs, we will measure acute care utilization, such as emergency department (ED) visits, total acute and ambulatory care-sensitive (ACS)-related hospitalizations. For MAA, we will also measure adherence to medications for common chronic conditions, such as hypertension and diabetes. See Table 2 for details on included effectiveness measures.

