## Outcomes and data analyses

To analyze our primary outcome, receipt of each EBP among top 10th percentile high-risk patients during the 18-month implementation period (Reach), we will model uptake of both practices in our Concurrent Stepped Wedge Design as a multilevel hierarchical model with a repeated cross-sectional data structure in which sites are followed over time. In this design, the data structure includes patients at level 1 (where Reach, the main outcome of interest, in measured), nested within time at level 2, and nested within sites at level 3. The main predictors will be site implementation strategy assignment (EBQI-IC vs. EBQI-LC vs Usual Care) over time (measure as the number of quarter). We will first describe differences in trends using unadjusted analyses, then add covariates for patient characteristics (i.e., age, sex, Elixhauser comorbidity score [66]) and site-level covariates (i.e., number of unique patients served in primary care, rural vs urban). Secondary analyses of Reach will include models by key patient subgroups, including those hospitalized in the 90 days prior to the quarter examined, and models with an interaction term for assigned implementation strategy by EBQI fidelity level (as defined above), to examine how implementation strategy fidelity may have impacted Reach.

To analyze our secondary outcomes of care processes, patient experiences, provider experiences, and performance measures (Effectiveness), we will first model unadjusted trends in outcomes over time for each EBP, by site implementation strategy assignment. We will then model outcomes using two or three-level (depending on whether the metric is measured at the patient or site level) hierarchical models based on the concurrent Stepped Wedge Design using repeated cross-sectional data, adjusted for the same covariates included in the models for our primary outcome. In models of medication adherence, we will add covariates for medication regimen complexity, as indicated by total number of classes of medication prescribed for the condition of interest, and patient co-pay status. If we find differences in outcomes, we will perform mediation analyses that consider how Reach and EBP fidelity may have mediated outcomes [67].

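### Sites are targeted on ACS hospitalization rate, which is also an outcome compared with the same sites' usual-care time, so regression to the mean can bias the EBQI-versus-usual-care estimate for acute care

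*Protocol article*

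**What the plan says.** Four statements in the protocol article bear on this point.

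- **Selection** (Site selection and eligibility): "We will implement the EBPs at 16 primary care sites, targeting those with high ambulatory care-sensitive hospitalization rates". No selection window, cut-off or candidate pool is given.
- **Comparator** (same section): "Time periods without active implementation will serve as the usual care periods for EBQI strategies". All sites are implementing sites: "Site implementation consists of four overlapping cohorts of four sites (three randomized to LC and one to IC"), and "all will undergo 18-months of RIVET facilitation". No never-implemented site is described. What is randomized is the strategy: "Implementation strategies are randomized by site". Random assignment of start time is not stated.
- **Outcome** (Effectiveness): "For both EBPs, we will measure acute care utilization, such as emergency department (ED) visits, total acute and ambulatory care-sensitive (ACS)-related hospitalizations". Table 2 lists "VHA ACS-related and total acute hospitalizations" in the CACP row only, a small inconsistency with the text.
- **Model** (Outcomes and data analyses): the primary model is described as "The main predictors will be site implementation strategy assignment (EBQI-IC vs. EBQI-LC vs Usual Care) over time (measure as the number of quarter"). Effectiveness outcomes use hierarchical stepped-wedge models with the same covariates: age, sex, Elixhauser score, number of primary care patients, and rurality. Neither a baseline ACS rate nor any handling of the selection period is named.

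**The concern.** A site picked because its observed rate is high has, on average, a true rate below the observed one. The chance excess disappears in later quarters whatever EBQI does. If the quarters that triggered selection are analysed as usual care and the later ones as EBQI, that fall is credited to EBQI.

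At stake is the EBQI-versus-usual-care estimate for ACS hospitalizations. Total hospitalizations and ED visits are affected only so far as they move with the ACS rate. The mediation analyses would carry a false difference forward, but they are planned only if differences are found.

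**Working it through.** **No figure to reproduce.** The article gives no site rates, effect size or power calculation. The only arithmetic check is 4 cohorts × 4 sites = 16 sites, of which 4 × 3 = 12 are LC and 4 × 1 = 4 are IC. This agrees. Everything below rests on assumed inputs.

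**Simple formula, close to a worst case.** Suppose usual care consisted of nothing but the selection window. With z the mean standardized observed rate of the chosen sites, CV the observed between-site coefficient of variation and r the reliability of the rate, the expected rate ratio with no true effect is (1 + z·CV·r)/(1 + z·CV).

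- Top quarter of sites, z = 1.27. CV 0.2: r = 0.6 gives (1 + 0.1524)/(1.254) = 0.919, and r = 0.8 gives 0.959. CV 0.3: 0.890 and 0.945.
- Top half, z = 0.80, same CV and r: 0.923 to 0.972.

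Usual care would normally include other quarters, which dilutes this. In one simulation with one-time selection, four earlier quarters plus waiting quarters, and no time term, the artefact was about 36–41% of the formula's value.

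**Null simulation.** There was no true EBQI effect. Assumptions: 130 candidate sites, mean rate 100, true between-site SD 20, selection on a four-quarter mean, independent quarterly noise, cohorts starting two quarters apart, site effects in the model, post-implementation time dropped. Entries are the LC-versus-usual-care coefficient in index points at reliability 0.5 / 0.7 / 0.9. Negative means false benefit.

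| Site selection | Targeting quarters in usual care? | Time term | False effect |
|---|---|---|---|
| Once | Yes | None | −13.8 / −6.9 / −2.1 |
| Once | Yes | Linear, 8 pre-start quarters | −11.5 / −5.7 / −2.1 |
| Once | Yes | Categorical quarter | +0.5 / −0.3 / 0.0 |
| Once | No | None | −0.7 / −0.3 / +0.2 |
| By cohort | Yes | None | −15.8 / −7.6 / −1.9 |
| By cohort | Yes | Linear | −45 / −24 / −8 |
| By cohort | Yes | Categorical quarter | −49.2 / −25.9 / −9.2 |
| By cohort | No | Categorical quarter | +16.5 / +10.7 / +5.9 |

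Four points follow.

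1. With one-time selection, categorical quarters remove the bias. Later cohorts, chosen by the same rule and still waiting, show the same fall at the same calendar time.
2. A linear term is not a dependable substitute. Under one-time selection it gave about zero with four pre-start quarters, but left the bias in the table with eight.
3. With cohort-by-cohort selection the excess sits just before each site's own start, so calendar time cannot absorb it. Excluding the window then errs toward harm. The likely reason is that a site not chosen for an earlier cohort tended to have lower rates in those earlier quarters, and these remain as its usual care.
4. Excluding the window is not sufficient alone. With one-time selection, no time term and AR(1) noise of 0.5, −4.7 / −2.5 / −1.1 remained.

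The LC-minus-IC difference stayed between about −1.5 and +2.8, mostly within simulation error.

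**The case against.** The strongest reply is that the bias depends on facts the article does not give: when the ACS rates were measured, whether sites were chosen once or by cohort, when usual-care data begin, and the form of the time term. A condensed article may leave such detail to a fuller plan, and in one plausible configuration the stepped-wedge model already removes the problem. The trial is also a type 3 hybrid whose aim is IC versus LC on Reach. All of this stands and limits the point. It does not dispose of it, because the article does fix the selection rule, the comparator and the outcome, and these three together create the exposure.

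A reader might infer more than the document supports:

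- **That the fall will appear as an EBQI benefit, or that no time adjustment can help.** The third row of the table shows otherwise.
- **That the artefact matches or exceeds the effect sought.** That comparison needs an invented Reach, the cited geriatric-assessment readmission odds ratio (0.88) read as a rate ratio, and the near-worst-case formula.
- **That the cost results inherit the bias.** The Return-On-Investment section describes a patient-level contrast of exposed with unexposed patients, not this site-level estimate.

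The selection rate and the outcome may also differ in population (whole site versus high-risk patients). That would weaken the bias without abolishing it.

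**Conclusion.** The point holds in conditional form. The direction is usually toward benefit if targeting quarters count as usual care. Under the assumptions above, the false effect is about zero with one-time selection and categorical calendar quarters. It is up to about 14 index points with one-time selection and no time term, and about 9 to 49 with cohort-by-cohort selection and categorical quarters. These figures illustrate the mechanism and are not estimates for this trial, whose actual bias cannot be sized from the document. The matter is a secondary comparison; Reach and IC versus LC are essentially untouched. It is worth correcting because the remedy is specific and cheap.

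**What to change.** For hospitalization and ED outcomes, add to the analysis plan:

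1. State when ACS rates were measured for targeting, and whether sites were chosen at one time or cohort by cohort.
2. Model calendar quarter as categorical.
3. Exclude from usual care the quarters whose ACS rates were used to target each site, and draw earlier usual-care quarters from the VHA data warehouse.
4. Report the EBQI-versus-usual-care estimate with and without those quarters.
5. If selection was cohort by cohort, treat the two estimates as a bracket, since the one without the targeting quarters can err toward harm. Claim a reduction in acute care use versus usual care only if both agree.

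The cost is a few sentences, an earlier data extract, fewer usual-care quarters just before each start, and some loss of precision.
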